### Independent/exposure variables and confounding

In both groups, the main exposure variable shall comprise pharmacological management. The impact of each management on the trial endpoints shall be controlled for confounding variables: concomitant medications or co-intervention at an outside facility or by another provider.

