**Methods/Design:**

A PROBE (prospective randomized open blinded endpoint) parallel-group design will be used. Adult patients with a diagnosis of reduced ejection fraction HF, who are being treated at a specialized HF clinic are being recruited. Those with indications for loop diuretic dose adjustment during routine clinic visits will be randomized to take part in the trial. Participants in the intervention group (IG) shall have their diuretic doses adjusted in accordance with the AAD and receive four telephone calls (one per week) over 30 days to reinforce guidance on nonpharmacological management (fluid and sodium restriction). Participants in the control group (CG) shall have their diuretic doses adjusted by a physician during the first trial visit and shall not receive any telephone calls. Patients in both groups shall return at 1 month for face-to-face reassessment. The study endpoints shall comprise readmission and/or emergency department visits due to HF decompensation within 90 days and clinical instability. All participants shall be required to have a scale at home (or easy access to one), a telephone number, agree to telephone-based follow-up, and be available to return for a 1-month trial visit. Overall, 135 patients are expected to be enrolled in each group.

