### Study protocol

Participants randomized to the CG shall have their diuretic dose adjusted at the physician’s discretion. These patients will not receive telemonitoring, but will return for 30-day clinical reassessment.

Participants randomized to the IG shall receive telemonitoring with the AAD for dose adjustment and CCS for assessment of signs and symptoms of decompensation and body weight fluctuations. Telephone calls shall take place once weekly for a total of four calls during the 1-month intervention period. First, the calling nurse shall enquire as to the presence of signs and symptoms of deterioration (paroxysmal nocturnal dyspnea, orthopnea, fatigue during activities of daily living (for functional class assessment), lower extremity edema, vomiting or diarrhea, dizziness or syncope, and body weight fluctuations) during the preceding week. Depending on the signs and symptoms reported, the patient shall receive guidance according to one of the following algorithm pathways: weight remained within the expected range (change in body weight <1 kg), weight loss was greater than expected (weight loss ≥1 kg), or weight gain was greater than expected (weight gain ≥1 kg). Guidance shall be provided in accordance with the patient’s individual needs regarding adherence to pharmacological and nonpharmacological management. A face-to-face reassessment shall be conducted at 30 days by a nurse blinded to group allocation. At each telephone contact/reassessment, the AAD shall be administered again to guide diuretic dose adjustment.

Data on clinical and sociodemographic parameters shall be collected from all participants in both groups, with the CCS used to assess clinical condition.

During clinic visits, all patients are provided routine guidance on HF, including information on pharmacological management (regular use of prescribed medications and their effects) and nonpharmacological management (weight management, fluid and sodium restriction, physical activity), and any questions they may have are answered.

At the 30-day visit, all patients shall undergo reassessment by means of the CCS and recollection of data on all variables of interest.

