At 90 days, the study endpoint (readmission or emergency department visit, change in CCS, deterioration in NYHA functional class, and HF-related mortality) shall be assessed by means of a chart review, consisting of an analysis of patients’ records. Patients who sought care at an outside facility shall be asked to provide their progress notes or discharge summary. Chart-based endpoints are expected to be confirmed by telephone contact with participants in both groups (Figure 1).

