**Flowchart of study participation and interventions.**

### Randomization

During a physician- or nurse-led clinic visit in which a need for adjustment of loop diuretic (furosemide) doses is identified, the patient shall be tested for trial eligibility by the investigator. Patients who meet the eligibility criteria shall be invited to take part in the study, and those who accept will provide written informed consent. Clinical assessment and sociodemographic and clinical data collection shall take place before randomization. The investigator shall then report to the team member (not involved in the trial) in charge of the randomization list. Specific software shall be used for participant allocation into IG and CG by sequential random number generation.

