### Sociodemographic and clinical variables

A structured questionnaire shall be administered to all trial participants for collection of data on sociodemographic and clinical parameters (age, sex, educational attainment, income, current prescriptions, comorbidities, smoking, alcohol intake, etiology of HF, duration of HF, prior admissions, echocardiographic findings, and serum sodium, potassium, urea, and creatinine levels). Weight, vital signs, presence of crackles, third heart sound, jugular venous distension, peripheral edema, history of orthopnea, hepatojugular reflux, hepatomegaly, and NYHA functional classification shall be assessed during the history and physical examination. Patients shall be instructed to measure their body weight daily, in the morning, after urination, while lightly clothed and before their first meal of the day. Patients will be required to use the same scale throughout the study period and calibrate (tare) it with 1 kg before body weight monitoring [17].

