### Statistical analysis

Continuous variables shall be expressed as means and standard deviations if normally distributed or medians and quartiles otherwise. Categorical variables shall be expressed as absolute and relative frequencies. Depending on the distribution of variables, baseline characteristics and the effect of the trial intervention shall be compared by means of Student’s *t-*test or the Mann-Whitney *U* test (for continuous variables) or Pearson’s chi-square test (for categorical variables). A *P* value <0.05 (two-tailed) shall be considered statistically significant. Intention-to-treat analysis shall be employed for all patients who meet a trial endpoint before 90 days. All statistical analyses shall be carried out in Statistical Package for the Social Sciences (SPSS) 18.0.

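### The plan calls for control for outside co-intervention, a variable that arises after randomisation, and this does not match its own unadjusted, intention-to-treat analysis

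*Protocol article*

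**What the plan says.** All references are to the protocol article.

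- **Independent/exposure variables and confounding.** "In both groups, the main exposure variable shall comprise pharmacological management". The impact of each management on the endpoints "shall be controlled for confounding variables: concomitant medications or co-intervention at an outside facility or by another provider". No time point is given for either variable, and no model.
- **Study protocol, 90-day paragraph.** Outside care is gathered when the endpoint is ascertained: "Patients who sought care at an outside facility shall be asked to provide their progress notes or discharge summary".
- **Sociodemographic and clinical variables; Randomization.** The questionnaire covers "age, sex, educational attainment, income, current prescriptions, comorbidities" and more. On timing: "Clinical assessment and sociodemographic and clinical data collection shall take place before randomization".
- **Study protocol, 30-day visit.** "all patients shall undergo reassessment by means of the CCS and recollection of data on all variables of interest".
- **Abstract, Methods/Design.** Besides dose adjustment by the algorithm, the intervention group is to "receive four telephone calls (one per week) over 30 days to reinforce guidance on nonpharmacological management".
- **Statistical analysis.** "baseline characteristics and the effect of the trial intervention shall be compared by means of Student’s" t-test, the Mann-Whitney test or Pearson's chi-square test. Intention-to-treat is named, in a sentence that ties it to patients who reach an endpoint within 90 days. No covariate model appears.

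**The concern.** Randomisation removes systematic confounding of the comparison between arms. A variable that arises afterwards cannot confound that comparison. It can be a consequence of allocation, and if disease severity also drives it, conditioning on it does two things. It removes whatever part of the effect runs through it, and it makes the arms unequal in severity within its levels.

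Co-intervention by outside providers fits this description. The arms are open, only the intervention group is called weekly, and the trial's stated mechanism is to catch deterioration early so that emergency visits and readmissions fall. An outside emergency visit for decompensation is an endpoint event, and it could also be coded as an outside co-intervention. To that extent the outcome would be adjusted for itself.

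Two looser points sit in the same paragraph. The exposure is described as pharmacological management, although the randomised contrast also includes telephone reinforcement of nonpharmacological care. And concomitant medications could mean values before or after randomisation. With this paragraph and the Statistical analysis section both in force, an analyst could choose between an unadjusted and an adjusted result once the data are known.

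**Working it through.** **The plan's own figures.** There is none to reproduce on this point. The 270 patients come from an unadjusted comparison and do not depend on it.

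**Timing of each variable.**

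- *Outside or other-provider co-intervention.* It is not named among the items collected before randomisation. As something alongside the trial treatment, it can only occur after allocation.
- *Concomitant medications.* Current prescriptions are recorded before randomisation, and adjusting for those is legitimate. The variables of interest are collected again at day 30, and adjusting for those values is not. The text does not say which is meant.

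**Illustration 1: odds ratio scale.** The documents give no control event rate and no rate of outside care, so every input here is an assumption. Let T be arm (1 = intervention), U a standard normal unmeasured severity, C co-intervention and Y the endpoint:

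- logit P(C=1) = −1.2 + sU + aT
- logit P(Y=1) = −1.0 + sU + bT + 0.8C
- loss = 1 − ln(OR adjusted for C) / ln(OR unadjusted)

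The model was solved by numerical integration over U:

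| a | b | s | C: control vs intervention | OR unadjusted | OR adjusted | Loss of log OR |
|---|---|---|---|---|---|---|
| −0.8 | −0.4 | 1 | 27% vs 16% | 0.665 | 0.775 | 37% |
| −0.4 | −0.4 | 1 | 27% vs 21% | 0.695 | 0.743 | 18% |
| −0.4 | −0.4 | 0.5 | 24% vs 18% | 0.656 | 0.693 | 13% |
| 0 | −0.4 | 1 | 27% vs 27% | 0.730 | 0.707 | none |
| −0.8 | 0 | 1 | 27% vs 16% | 0.918 | 1.093 | sign reversed |
| −0.8 | 0 | 0.5 | 24% vs 13% | 0.909 | 1.027 | sign reversed |

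First row: ln 0.665 = −0.408 and ln 0.775 = −0.255, so the loss is 1 − 0.255/0.408 = 0.37. The event rates in that row are 35% and 26%. Simulated runs of the same model agree within sampling error: 0.664 to 0.776 (38%) for the first row and 12% for the third.

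In the fourth row the odds ratio moves slightly away from 1. That is expected when a prognostic covariate enters a logistic model, and it is not attenuation.

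**Illustration 2: risk difference, true effect zero.** This was a simulation of 1,000,000 patients with an assumed control event rate of 34%. The unadjusted difference is about 0.000. After adjustment for a co-intervention that depends on arm and severity:

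- co-intervention about 40% vs 31%: +0.015
- about 40% vs 22%: +0.029
- about 40% vs 16%: +0.040
- equal in both arms: about 0.001

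For scale, the protocol's 20% relative reduction at that assumed rate would be 0.34 × 0.20 = 0.068. The spurious difference is therefore 0.015/0.068 = 22% to 0.040/0.068 = 59% of the target effect, in the direction of harm.

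**The case against.** The strongest reply is that no adjusted model exists. The Statistical analysis section lists only two-group tests, and an article may leave to a fuller document how the control would be carried out. That limits the claim: nothing shows that an adjusted estimate would be primary. It does not remove the point, because the paragraph is a stated requirement, and a fuller plan could meet it for co-intervention only by contradicting it or by repeating the problem.

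Four stronger readings are tempting, and the documents do not support them.

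- A reader might infer that patients will be analysed by the management they received. The text does not say so. Each management can mean each arm's strategy, the analysis section compares the trial intervention, and no as-treated analysis is described. What stands is that allocated arm is not named and the telephone component is left out.
- A reader might infer that concomitant medications are post-randomisation values. No time point is given, and baseline prescriptions are available.
- A reader might take it as established that co-intervention lies on the causal path. The documents do not show that allocation changes outside care. It is a plausible inference from the open design and the calls in one arm.
- A reader might equate outside co-intervention with the endpoint. The endpoint is limited to readmission or emergency visits for decompensation, while co-intervention by another provider can include ordinary outpatient care. The overlap is partial.

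The illustrations also rest on chosen inputs, and 37–38% is the strong end of the range shown.

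**Conclusion.** The point holds in a limited form. The plan labels as a confounder, and requires control for, at least one variable that naturally arises after randomisation, that allocation can plausibly affect, and that partly overlaps the endpoint. Adjusting for it would not estimate the effect of assignment. The paragraph also leaves the timing of medications open, describes the exposure more narrowly than the randomised package, and does not match the unadjusted tests and intention-to-treat statement in the Statistical analysis section.

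The size cannot be fixed from the documents. Under the assumptions shown, the loss of the log odds ratio is none if the arm does not affect co-intervention, 12–18% with moderate inputs and 37–38% with strong ones. Among the scenarios run, the sign reversed only where the algorithm had no direct effect. By continuity, a direct effect close to zero would behave the same way. This is a reconciliation of two sections that should be made before analysis. It is not evidence that the planned unadjusted comparison is biased.

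**What to change.** Reconcile the section on exposure variables and confounding with the Statistical analysis section:

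1. State that the exposure is randomised arm (intervention group versus control group), meaning allocation to the whole package, including the telephone component.
2. State that the primary comparison is by allocated arm in all randomised patients.
3. Limit any adjustment to pre-randomisation variables already collected, for example baseline Clinical Congestion Score, NYHA class, prior admissions and current prescriptions, each specified as the baseline value.
4. Report post-randomisation medication and outside or other-provider co-intervention descriptively by arm, or use them only in a supplementary analysis labelled as such.

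The cost is the rewording of one paragraph, plus a sentence in the analysis section. No new data are needed and the sample size stays at 270. When the article was written, 66 patients had been enrolled and recruitment was open.

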### Statistical analysis

Continuous variables shall be expressed as means and standard deviations if normally distributed or medians and quartiles otherwise. Categorical variables shall be expressed as absolute and relative frequencies. Depending on the distribution of variables, baseline characteristics and the effect of the trial intervention shall be compared by means of Student’s *t-*test or the Mann-Whitney *U* test (for continuous variables) or Pearson’s chi-square test (for categorical variables). A *P* value <0.05 (two-tailed) shall be considered statistically significant. Intention-to-treat analysis shall be employed for all patients who meet a trial endpoint before 90 days. All statistical analyses shall be carried out in Statistical Package for the Social Sciences (SPSS) 18.0.

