### Endpoints

The endpoints include hospital readmission and/or emergency department visits due to HF decompensation within 90 days, two-point change in CCS, and deterioration of NYHA functional class. The secondary outcome shall be a composite of the aforementioned primary endpoints and 90-day HF-related mortality.

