## Discussion

Patients in the intervention group (IG) and control group (CG) undergo routine assessment during physician or nurse visits by means of the CCS. This instrument tests for and scores the presence of crackles, elevated central venous pressure, jugular venous distension, third heart sound, orthopnea, hepatojugular reflux, and peripheral edema. It also assesses functional class by means of the New York Heart Association (NYHA) Functional Classification scale. Total scores range from 1 to 22. Scores ≥5 were found to be associated with congestion in a study of the clinical applicability of the AAD [14].

Data are also collected on weight, height, history of present illness, past medical history, comorbidities, echocardiographic findings, current prescriptions, sex, age, skin color, educational attainment, and household income. Laboratory parameters (serum sodium, potassium, urea, and creatinine levels) shall be recorded at randomization. If diuretic dose adjustments are required on two consecutive visits, a further battery of these tests shall be ordered.

Patients shall be instructed to return at 30 days for a face-to-face assessment visit.

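### The CCS endpoint is worded in two ways and tested without baseline CCS; analysing the 30-day score by ANCOVA would use the same data more precisely

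*Protocol article*

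**What the plan says.** The Endpoints section of the protocol article lists, beside HF readmission or emergency visits, "two-point change in CCS, and deterioration of NYHA functional class", and then refers back to these as primary endpoints. It does not say whether the two points are an improvement or a worsening. The Study protocol section lists what is assessed at 90 days as "readmission or emergency department visit, change in CCS, deterioration in NYHA functional class, and HF-related mortality", with no cut-point for CCS.

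The Statistical analysis section says that "baseline characteristics and the effect of the trial intervention shall be compared by means of" Student's t or the Mann-Whitney test for continuous variables and Pearson's chi-square for categorical ones. The section on exposure variables and confounding adds that the effect "shall be controlled for confounding variables: concomitant medications or co-intervention at an outside facility or by another provider". It names no method, and baseline CCS is not among the factors.

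On the data available, the Randomization section says "Clinical assessment and sociodemographic and clinical data collection shall take place before randomization". The Study protocol section makes CCS part of the assessment in both groups and repeats it in all patients at the 30-day visit. The Discussion gives the scale: "Total scores range from 1 to 22".

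**The concern.** Two features of the plan cost precision.

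- If the two-point change is a yes/no outcome, it goes to chi-square. A patient who changes by two points then counts the same as one who changes by eight.
- If the change is kept as a number and compared by a t-test, the analysis forces a slope of 1 on baseline. When the true slope is lower, the change score carries baseline noise that ANCOVA removes.

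Improved clinical stability is one of the trial's two stated aims, and CCS is its main graded measure. A real effect on congestion could be missed, or estimated with a wider interval than the data allow. The two wordings also leave the choice between a cut and a score, and the direction of the cut, open until the data are in.

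**Working it through.** **The plan's own figures.** The only power statement is for readmission or emergency visit: 270 patients, 135 per arm, 20% attrition. No power, SD, correlation, responder share or expected difference is given for CCS, so there is no CCS figure to reproduce. The number of evaluable patients follows as 135 × 0.8 = 108 per arm. Alpha is 0.05, two-sided.

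**Assumed inputs.** Common SD of CCS; correlation ρ between baseline and 30 days (0.3 to 0.7); difference between arms; control share meeting the two-point cut (10% to 50%).

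**Step 1: relative efficiency in closed form.**
- The variance of the change is 2(1−ρ)SD², and the ANCOVA residual variance is (1−ρ²)SD². The efficiency of the change score against ANCOVA is their ratio, (1+ρ)/2: 0.65, 0.75 and 0.85 at ρ = 0.3, 0.5 and 0.7.
- Cutting a normal change at a point that a share p of patients meets keeps φ(z)²/[p(1−p)] of the information. At p = 0.5 this is 0.64. At p = 0.1 it is 0.1755²/0.09 = 0.34.
- The product is the efficiency of the cut change against ANCOVA: from 0.34 × 0.65 = 0.22 to 0.64 × 0.85 = 0.54.

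**Step 2: power where ANCOVA has 80%.** The standardised difference is d = 2.80 × √(2/108) × √(1−ρ²). At ρ = 0.5 this is 2.80 × 0.136 × 0.866 = 0.33.

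| ρ | d | t-test on change | chi-square on cut change (control share 10-50%) |
|---|---|---|---|
| 0.3 | 0.36 | 62% | 29-43% |
| 0.5 | 0.33 | 68% | 33-49% |
| 0.7 | 0.27 | 73% | 37-54% |

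The relative loss for chi-square runs from (80−54)/80, about 33%, to (80−29)/80, about 64%. For the t-test on the change it is 7 to 18 percentage points.

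**Step 3: simulation on the actual scale.** Integer scores were clipped to 1-22, with assumed means of 8 at baseline and 6.5 at 30 days in controls, 108 per arm and 3,000 trials per row. Power:

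| SD, difference, ρ | chi-square, worsening ≥2 | chi-square, improvement ≥2 | t-test on change | ANCOVA |
|---|---|---|---|---|
| 3, 1, 0.5 | 33% | 47% | 66% | 80% |
| 3, 1, 0.3 | 29% | 36% | 53% | 71% |
| 4, 1.3, 0.5 | 38% | 42% | 61% | 77% |
| 3, 1, 0.7 | 38% | 67% | 86% | 92% |

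Repeat runs move single entries by up to about 3 points.

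Hand check of the first row:
- The ANCOVA standard error is 3 × 0.866 × 0.136 = 0.354. Then 1/0.354 − 1.96 = 0.87, which is 81% power.
- The standard error of the change is 3 × 1 × 0.136 = 0.408. Then 1/0.408 − 1.96 = 0.49, which is 69% power.
- Both sit slightly above the simulated values, which also carry rounding and clipping.

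**Step 4: larger effects.** With a difference of 1.5 (SD 3), chi-square on improvement reaches 80% against 99% for ANCOVA at ρ = 0.5, and 95% against 100% at ρ = 0.7. The gap narrows.

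The order is the same in every setting: chi-square, then the t-test on the change, then ANCOVA.

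**The case against.** The strongest reply is that the dichotomy is only one reading. The Endpoints section does not say proportion or responder, the Study protocol section gives no cut, and the Statistical analysis section provides tests for continuous variables. This stands. A reader might infer that the plan definitely tests a dichotomised CCS, but the article does not settle it. On the continuous reading the loss is the smaller one in the t-test columns.

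Second, the direction of the cut matters. Patients enter because their diuretic needs adjusting, so under the assumed fall in mean CCS worsening is uncommon and an improvement cut loses less. This stands too, which is why both directions are shown.

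Third, the analysis is not wholly unadjusted, and baseline is not ignored: the confounding section promises some adjustment, and a change already contains the baseline value. That is correct, but the promised adjustment covers concomitant medications and co-interventions, some of which can arise after randomisation. A change score uses baseline less efficiently than a covariate does.

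Fourth, an unadjusted comparison in a randomised trial is valid, covariate lists commonly sit in a statistical analysis plan, and CCS did not size the trial. All true. The point is therefore one of precision and of wording that the article itself leaves inconsistent. It alleges no bias and does not touch the stated 80% power.

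**Conclusion.** The point holds as an efficiency and consistency point. The CCS endpoint is worded in two ways, its direction is unstated, and no named test or adjustment uses baseline CCS as a covariate although it is collected before randomisation.

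Under the assumed values (108 per arm, SD 3 to 4, difference 1 to 1.3, ρ 0.3 to 0.7), ANCOVA power of about 71-92% falls to about 51-86% with a t-test on the change. With chi-square it falls to about 35-67% (improvement cut) or 28-40% (worsening cut). The loss shrinks for larger effects. It also shrinks with higher correlation for the change score and the improvement cut. For the worsening cut it does not in these runs, because worsening then becomes rarer.

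Three stronger statements are tempting and not supported:
- That the plan gives away up to half its power. No CCS input is documented, and half is not a ceiling: 29% against 71% is a loss of about 59%.
- That the trial is already underpowered on its sized endpoint. This depends on a control event rate the article does not state. A 20% relative reduction gives about 270 patients at a control rate near 83%, and needs about 970 at 50%.
- That clinical stability is the question this trial could answer well. No CCS effect or SD is given from which to judge that.

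**What to change.** Use one definition of the CCS endpoint in the Study protocol, Endpoints and Statistical analysis sections, with its time point. Prespecify 30-day CCS as a score, analysed by ANCOVA with randomised group and baseline CCS, and report the difference with a 95% confidence interval. Keep the two-point change, with its direction stated, as a descriptive responder summary by arm.

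A baseline-adjusted model for readmission or emergency visits is optional; no gain has been quantified for it here.

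The cost is wording only. The measurements are already scheduled, the model runs in the named SPSS package, and no visit or patient is added. With 66 of 270 patients enrolled and 58 completed at the time of writing, the change should be made before any comparison between arms is seen.

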### Sample size

Sample size was estimated in the WinPepi 11.1 software suite, using readmission or emergency department visit within 90 days of randomization as the endpoint [16]. Considering a 20% relative reduction in readmissions or emergency department visits in the intervention group, a significance level of 0.05, a statistical power of 80%, and an attrition rate of 20%, the sample size was set at 270 patients (135 in each group).

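### The 90-day event comparison is an unadjusted chi-square, leaving recorded baseline predictors unused, while the only adjustment stated is for factors that can arise after randomisation

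*Protocol article*

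**What the plan says.** All references are to the protocol article.

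- **Test.** Statistical analysis: "baseline characteristics and the effect of the trial intervention shall be compared by means of" Student's t-test or Mann-Whitney for continuous variables, and Pearson's chi-square for categorical ones. Significance is two-tailed at 0.05.
- **Endpoint that sizes the trial.** Sample size: "using readmission or emergency department visit within 90 days of randomization as the endpoint". This is a yes/no outcome, so the test that applies is the chi-square.
- **Baseline data.** Sociodemographic and clinical variables lists, among others, "etiology of HF, duration of HF, prior admissions, echocardiographic findings, and serum sodium, potassium, urea, and creatinine levels", and adds NYHA class at the physical examination. Study protocol says the CCS is used to assess clinical condition in both groups. Discussion says the CCS also covers functional class and that laboratory values are recorded at randomisation.
- **Timing.** Randomization: "Clinical assessment and sociodemographic and clinical data collection shall take place before randomization".
- **Adjustment.** Independent/exposure variables and confounding promises that effects on the endpoints will be controlled for other medication and for care received elsewhere or from another provider. It names no baseline severity variable and no model.

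**The concern.** None of the three named tests can carry a covariate. Variables that plausibly predict heart-failure readmission are therefore collected on everyone and then left out of the comparison they could sharpen. This is a stated choice of test, not a detail passed over in silence.

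The confounding section makes matters worse. It promises adjustment that the analysis section has no method to deliver, and the variables it names can change after allocation. The arms differ in how diuretics are managed and in telephone contact, so later prescriptions and outside care may themselves be affected by the arm. Conditioning on them can bias a randomised comparison; conditioning on baseline values does not carry that risk.

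At stake are some precision in the main estimate, and an unclear rule on which variables may enter it.

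**Working it through.** **1. The plan's own figure.** Stated inputs: "a significance level of 0.05" (two-tailed in Statistical analysis), 80% power, 20% attrition, 270 patients (135 per group), and "Considering a 20% relative reduction in readmissions or emergency department visits in the intervention group". No control-arm event rate is given, so 135 per group cannot be reproduced. With the usual two-proportion formula (pooled variance under the null, no continuity correction) and division by 0.8 for attrition, the need per group is:

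| Assumed control rate | Per group |
|---|---|
| 30% | 1074 |
| 40% | 705 |
| 50% | 485 |
| 70% | 233 |

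The stated 135 is reached only near an 85% control rate, with continuity correction (108/0.8 = 135). Evaluable patients after attrition: 135 × 0.8 = 108 per arm, 216 in all.

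**2. Gain from adjustment if the trial truly had 80% power.** Let R² be the share of outcome variance explained by baseline covariates. It is not in the article; 0.02 to 0.25 is assumed. Adjustment multiplies the variance of the effect estimate by (1 − R²), so

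power = Φ[(1.960 + 0.842)/√(1 − R²) − 1.960], and equivalent evaluable patients = 216/(1 − R²).

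| R² | Power | Equivalent of 216 |
|---|---|---|
| 0.02 | 80.8% | 220 |
| 0.05 | 82.0% | 227 |
| 0.10 | 84.0% | 240 |
| 0.15 | 86.0% | 254 |
| 0.20 | 87.9% | 270 |
| 0.25 | 89.9% | 288 |

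Example, R² = 0.10: 2.802/0.949 = 2.953; 2.953 − 1.960 = 0.993; Φ(0.993) = 84.0%.

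**3. Gain at the planned effect.** With 108 per arm and an assumed 40% vs 32%, unadjusted power by formula is 23.0%. Trials were also simulated with four assumed predictors (odds ratios, weaker/stronger set): prior admission 2.0/2.5, CCS per SD 1.4/1.7, NYHA III/IV 1.5/2.0, creatinine per SD 1.3/1.5. The joint c-statistic is 0.65 to 0.72. Three independent sets of runs (4,000, 4,000 and 8,000 trials per scenario) gave, unadjusted to adjusted:

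| Run | Weaker predictors | Stronger predictors |
|---|---|---|
| 1 | 24.2% to 24.8% | 23.8% to 25.3% |
| 2 | 23.6% to 24.5% | 23.2% to 26.5% |
| 3 | 23.3% to 24.1% | 23.8% to 26.3% |

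The gains run from 0.6 to 3.3 points. In run 1 the unadjusted type I error was 4.6% to 4.7% and the adjusted 4.9% to 5.4%.

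**4. Do steps 2 and 3 agree?** Run 1 put the effective-sample gain at 6% to 13%, measured at 40% vs 24%. That corresponds to R² of 1 − 1/1.06 = 0.06 to 1 − 1/1.13 = 0.12. Putting these into the step 2 formula from 23.0% gives 24.2% to 25.6%, in line with the simulations. Only the extreme R² of 0.25 would reach 29.2%.

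**5. Sections side by side.** The analysis section names tests without covariates. The confounding section promises control for other medication and outside care. Other medication may overlap the current prescriptions recorded at baseline, but outside care during follow-up cannot be a baseline value. As written, the two sections cannot both be carried out.

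**The case against.** The strongest reply is that an unadjusted chi-square in a randomised trial is valid, that a condensed article often leaves covariate lists to a fuller document, and that the analysis sentence is generic and does not rule out an adjusted analysis. Validity stands in full. The appeal to a fuller document stands only in part: the article does state which tests compare the intervention effect, and it states an adjustment that those tests cannot perform.

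Four stronger readings are tempting, and the article does not support them.

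- *That no adjustment is planned.* The confounding section promises some, and other medication could include baseline prescriptions. The fault lies in which variables it names and in the missing model.
- *That chance imbalance biases the result.* Imbalance arising by randomisation is already covered by the test's error rate, as the null runs show.
- *That allocation is unstratified.* The Randomization section describes software-generated random numbers and is silent on strata. In an article, silence is not proof of none.
- *That adjustment buys a large gain.* Under the same assumptions, power at 40% vs 24% rises from about 71–72% to 74–77% (run 1). But that is a 40% relative reduction, since 24/40 = 0.60, and the plan assumes 20%.

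It is also fair to say that how well these variables predict events in a single-clinic cohort, all needing a diuretic change, is unknown.

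**Conclusion.** The point holds as a modest loss of efficiency together with an inconsistency between two sections. The named test for the sizing endpoint ignores prior admissions, CCS and creatinine, all available at or before randomisation. The only stated adjustment targets variables that can arise after it and has no model.

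The gain from correcting this is about 1 to 10 points from a true 80% power for R² of 0.02 to 0.25. It is about 1 to 3 points from about 24% at an assumed 40% vs 32% with the simulated predictors. The control rate, R² and odds ratios are all assumptions. The simulations entered NYHA class separately from the CCS, so a list without it may gain somewhat less. Adjustment does not make up for the unstated control rate, which matters far more for power.

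**What to change.** - Make the main event analysis a logistic regression on randomised arm with a short covariate list: prior admission (yes/no), baseline CCS and creatinine. Do not enter NYHA class separately beside a CCS total that already contains it.
- Report the covariate-standardised risk difference and risk ratio with 95% confidence intervals. Keep the chi-square as a supporting analysis.
- Reword the confounding section so that the main comparison adjusts only for variables measured at or before randomisation. Describe later co-interventions by arm, or confine them to a sensitivity analysis.
- Fix the list before further outcome data are examined. Trial status reports 66 enrolled and 58 completed, so the choice should be dated and made without reference to their outcomes by arm.

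The cost is about a paragraph of wording, slightly more analysis work, some scripting for the standardised estimates, and a rule for missing baseline values. No new data or patients are needed.
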